### Process evaluation and satisfaction of the multicentre randomized controlled trial study implementation

Students, teachers, and principals will provide subjective evaluation reports of the program’s intervention components. During weeks 1, 6, and 12 of the intervention, students will be asked to rate the different active breaks (chosen by the classroom teacher) immediately after each participation, using a paper and pencil Likert scale ranging from “Hated it” = 1 to “Loved it” = 4.

At the end of the program, students will be asked to complete a questionnaire to rate their feelings about the activities performed, using a 4-level Likert scale with responses ranging from “strongly disagree” = 1, to “strongly agree” = 4 in the areas of: 1) enjoyment, 2) effect on learning and behaviour, 3) ability to perform activities, and 4) preferred duration and intensity. For example, “I enjoyed doing the active breaks” and “It was easier for me to concentrate after doing the active breaks.” Through focus groups conducted at the beginning and end of the intervention, students and teachers will provide additional feedback on their perception of the intervention program and video-guided active breaks. The focus groups will be guided by open-ended questions such as: “What did you like about doing active breaks?” and “Was there anything you did not like about doing active breaks?” The students’ responses will be complemented through writing and drawing activities. This process evaluation is based on the protocol developed by Watson et al. (2017b) for active break intervention in the classroom (Watson et al., 2017b).

### Measurement of perceived effort

Students will provide subjective evaluation reports of the intensity of intervention components of the program. During weeks 1, 6, and 12 of the intervention, students will be asked to rate the different active breaks. The EPInfant perceived exertion measurement scale has numerical descriptors (0–10), verbal descriptors and a set of illustrations that represent a child running at increasing intensities along a bar scale of incremental height (Rodríguez Núñez, 2016).

### Ethics committee

The study procedures will be conducted in accordance with the Declaration of Helsinki for Human Research (World Medical Association, 2013) and the ethical standards for physical activity and sports sciences (Harriss and Atkinson, 2011). The study protocol was approved by the Ethics, Bioethics, and Biosafety Committee of the University of Concepción prior to its execution (code: CEBB 1533-2023, September 2023). Additionally, after approval by the ethics committee, the clinical trial was registered in a clinical trial repository to ensure transparency in the analysis variables (add link once registered in the clinical trial).

### Statistical analysis

Missing data will be handled using intention-to-treat analysis (multiple imputation method) (Sterne et al., 2009). Descriptions will be performed as measures of central tendency and dispersion (continuous variables) and as percentages (categorical variables). Using the Shapiro-Wilk test, the normality of the data will be checked, and a two-step approach will be applied to transform non-normal variables (Templeton, 2011). Homoscedasticity will be analyzed using the Levene test. A two-way repeated measures analysis of variance (ANOVA) will be used to determine the effects of the interventions. The model effects are group (TG; CG), times (Pretest; Posttest), and their interaction over time (Time x Group). The Bonferroni *post hoc* test will be applied to identify statistically significant comparisons. Effect size (ES) will be determined using Cohen’s d (<0.2 insignificant; ≥0.2 and ≤0.49 small; ≥0.5 and ≤0.79 moderate; ≥0.8 large) (Cohen, 1988). Data will be analyzed using SPSS software (version 26 for Windows, IBM, New York, USA).

Missing data will be handled by a non-parametric missing value method using a random forest via the R package “missForest” of R statistical software (version 4.4.1). This function successfully imputes large and complex data sets of mixed type (quantitative and/or categorical variables), including complex interactions and non-linear relationships, using a random forest trained on observed values that predict missing values.

Mixed model analyses will be carried out to establish differences in school climate and mental health between the experimental group (video-guided active breaks incorporating curricular content within the school classroom setting) and the control group. The fixed effects of the model are group (Experimental versus control), times (Pretest; Posttest), and their interaction over time (Time x Group). The schools in the models will have a random effect to capture the hierarchical structure of the data and handle the possible dependence of observations within each school. To compare the probability of a model with the effect included versus a model with the effect excluded, the likelihood ratio test (LRT) will be used for the random effect. Additionally, the intraclass correlation coefficient (ICC) will be estimated to quantify the proportion of the total variance attributed to the variance between clusters (schools). Post-hoc tests will be performed using Holm’s correction for multiple comparisons. For all analyses, a significance level of *p* < 0.05 was established. Models will adjust for multiple covariates, such as demographic characteristics (e.g., age, gender) and secondary study variables, that could influence school climate and mental health outcomes. All analyses will be performed using Jamovi statistical software version 2.0.0.0 (The Jamovi Project).

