**Objective:**

This work outlines the design, measurements, intervention program, and potential efficacy of the “Active Classes + School Climate and Mental Health” project. This project will assess a 12-week program of active breaks through guided videos with curricular content in the school classroom, and its effects on mental health and school climate as its primary indicators. Additionally, it will measure physical activity, physical fitness, motor competence, and academic performance in students aged 6–10 years in the Biobío province, Chile, as secondary indicators. Methodology: A multicenter randomized controlled trial involving 823 students from 1st to 4th grade (6–10 years old), six schools (three intervention and three control) will be conducted in the Biobío region, Chile. Participants belonging to the intervention group will implement video-guided active breaks through the “Active Classes” web platform, featuring curricular content, lasting 5–10 min and of moderate to vigorous intensity physical activity, twice a day, Monday to Friday, over a span of 12 weeks. Expected Results/Discussion: To our knowledge, this will be the first study in Chile to evaluate the effects of incorporating video-guided active breaks with curricular content on mental health variables and school climate in schoolchildren. Thus, this study contributes to the scarce evidence on the effects of video-guided active breaks on mental health variables and school climate in schoolchildren worldwide. Additionally, it will provide crucial information about active teaching methodologies that have the potential to positively contribute to the wellbeing of students, thus addressing the problems of mental health and climate in Chilean schools. ClinicalTrials.gov ID NCT06423404.

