## Methodology

### Study design

This study adopts a multicenter, cluster, randomized, double-blind (evaluator and data analyst blind to each other) controlled trial design, with two arms, registered on ClinicalTrials.gov under the identifier NCT06423404, as of 20 March 2024. Six public educational centers in the Biobío region, Chile, were invited to participate (two from Biobío province, two from Arauco province, and two from Concepción province). The study followed the CONSORT guidelines for clinical trials (Butcher et al., 2022), reporting on social and psychological interventions (Montgomery et al., 2018), and the SPIRIT guidelines for protocol studies (Chan et al., 2013).

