### Study setting

This project targets public primary schools within the Biobío province, Chile, that share similar School Vulnerability Index (SVI) levels and fall within the medium to low socioeconomic bracket. The chosen schools are characterized by a daily schedule that spans roughly 8 hours (8:00 a.m. to 4:00 p.m.), segmented by two 15-min breaks (9:45 A, to 10:00 and 11:30 to 11:45 generally) and an extended 1-h lunch break (13:30 to 14:30). The study’s intervention specifically targets students in 1st to 4th grade. As can be seen in Figure 1, for the purposes of this research, six schools will be selected: half will participate in the intervention arm, while the other three will serve as the control group. This will result in a total sample size of approximately 820 students, assuming an average of eight classes per school, with each class comprising 30 to 40 students. All classes will continue with their physical education lessons, which correspond to 3 pedagogical hours per week according to the participating educational levels (See Figure 1).

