## Randomization of participating schools

After securing participation from schools, they will be randomly allocated to one of two groups through a sequence generated by the IBM SPSS software, ensuring concealed allocation. The groups are: 1) the Experimental Group (n = 3; 1 for each province), which will partake in a 12-week program of video-guided active breaks incorporating curricular content within the school classroom setting; and 2) the Control Group (n = 3; 1 for each province), which will receive the intervention after the conclusion of the initial data collection phase. This randomization allowed each province to have an experimental group and a control group. The random sequence will be kept confidential using sequentially numbered, opaque, sealed envelopes, managed by a researcher who will not interact with the schools or participants. Previous research with similar participant samples has identified significant differences in quality of life, motor skills, and academic performance, underscoring the potential impact of our intervention (Sánchez-López et al., 2019; Watson et al., 2017a).

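### Schools are randomised, but the repeated-measures ANOVA named to test the intervention treats pupils as independent and competes with the mixed model

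*Protocol article*

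**What the plan says.** The Study design section calls the trial cluster randomised: "This study adopts a multicenter, cluster, randomized, double-blind". The section Randomization of participating schools confirms the unit: "After securing participation from schools, they will be randomly allocated to one of two groups". Each arm has three schools, one from each province ("the Experimental Group (n = 3; 1 for each province" and "the Control Group (n = 3; 1 for each province").

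The Statistical analysis section then describes two ways of estimating the effect.

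- **Repeated-measures ANOVA (first paragraph).** "A two-way repeated measures analysis of variance (ANOVA) will be used to determine the effects of the interventions". The listed terms are group, time and Time x Group, with no school or class term. Follow-up comparisons use Bonferroni and the software is SPSS. The paragraph does not limit the ANOVA to any outcome.
- **Mixed model (last paragraph).** "Mixed model analyses will be carried out to establish differences in school climate and mental health between the experimental group". It tests the same Time x Group contrast, with a random effect for school to allow for dependence within schools. Follow-up comparisons use Holm. This paragraph says that all analyses are done in Jamovi.

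Neither analysis is named as the primary one.

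**The concern.** An analysis of a cluster trial has to judge the arm difference against variation between the units that were allocated. The ANOVA judges it against variation between pupils. If schools drift apart between pretest and posttest for reasons unrelated to the programme, that drift enters the arm contrast but hardly enters the error term. P-values come out too small, and any interval built on the same standard error is too narrow.

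Two consequences follow:

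- For school climate and mental health, two tests of the same contrast can disagree, and the article does not say which one decides. The result could be taken from the more favourable.
- For fitness, motor competence, physical activity and academic performance, the mixed model is not mentioned. The ANOVA is the only effect analysis the article offers.

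The mixed-model paragraph itself recognises dependence within schools, so the plan contradicts itself on whether clustering has to be handled.

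**Working it through.** **Inputs**

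- Clusters: 6 schools, 3 per arm (Randomization of participating schools).
- Pupils: the abstract has a trial "involving 823 students from 1st to 4th grade (6–10 years old), six schools". 823/6 = 137 per school.
- The Study setting section gives a "total sample size of approximately 820 students, assuming an average of eight classes per school, with each class comprising 30 to 40 students". This does not reproduce: 6 x 8 x 30 = 1,440 and 6 x 8 x 40 = 1,920, whereas 820/48 is about 17 per class. That is a separate matter. The stated total of 823 is used here because it gives the smaller clusters and so the milder result.
- Outcomes taken in two of the four grades, such as school climate (grades 3 and 4): about 137/2 = 68 per school, assuming equal grade sizes.
- Significance level: 0.05, taken as two-sided.
- ICC: the article gives no value, so a range is assumed. The relevant quantity is the ICC of the pre-post change, because stable school differences cancel.

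**Step 1: what the ANOVA tests.** With two groups and two time points, the Time x Group F statistic equals the square of the two-sample t statistic on change scores. Its error degrees of freedom are pupils minus 2, or 821.

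**Step 2: the true variance.** With m pupils per school and change-score ICC ρ, the variance of an arm mean is larger than the ANOVA assumes by the design effect

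DE = 1 + (m − 1)ρ.

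**Step 3: the true type I error of the nominal 5% test**

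α = 2[1 − Φ(1.96/√DE)].

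Worked example, m = 137 and ρ = 0.012: DE = 1 + 136 x 0.012 = 2.63; 1.96/√2.63 = 1.21; α = 23%.

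| ρ (assumed) | DE, m = 137 | α, m = 137 | DE, m = 68 | α, m = 68 |
|---|---|---|---|---|
| 0 | 1.00 | 5% | 1.00 | 5% |
| 0.005 | 1.68 | 13% | 1.34 | 9% |
| 0.012 | 2.63 | 23% | 1.80 | 14% |
| 0.025 | 4.40 | 35% | 2.68 | 23% |
| 0.05 | 7.80 | 48% | 4.35 | 35% |

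For m = 137 the effective number of pupils is 822/DE: 312 at ρ = 0.012, 187 at 0.025 and 105 at 0.05.

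**Step 4: simulation.** With 20,000 simulated trials per cell (3 v 3 schools, no treatment effect), the pupil-level test rejected in 5%, 13%, 23%, 35% and 49% of trials for m = 137, and in 5%, 9%, 15%, 23% and 35% for m = 68, in the row order of the table. A t-test on the six school means of change (4 degrees of freedom) rejected in about 5% in every cell.

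**Step 5: the mixed model as listed.** Its only stated random effect is for school. If that is an intercept constant over time, it adds the same amount to a school's pretest and posttest and drops out of the change. It then does not protect the Time x Group test from school-specific drift. Removing the ANOVA is necessary, but the model that remains also needs a term for that drift.

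**The case against.** Five points can be made for the plan.

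1. *The mixed model governs the primary outcomes and the ANOVA text is general or left over.* This is a fair reading, helped by the statement that all analyses run in Jamovi. On that reading the conflict over primary outcomes eases. The text does not say so, however, and the secondary outcomes would still have no clustered analysis.
2. *The article does not expressly assign the ANOVA to secondary outcomes, and an analysis plan not shown might assign models by outcome.* Correct. What can be said is that the article names no clustered analysis for them. The fault is not an omission, though: the article states a specific model that does not fit the design.
3. *The size rests on an assumed ICC.* Also correct. At zero the test is valid, and at 0.005 the error is 9% to 13%. How far above 5% the error lies is unknown.
4. *Province blocking and similar schools reduce the problem.* Change shared by both schools of a province cancels from the arm contrast. If half of the school variance were shared in this way (an assumption), the figures for m = 137 fall from 23%, 35% and 48% to about 15%, 23% and 35%. The error is smaller but still well above 5%.
5. *The two cluster sizes do not cover every outcome.* Reading is tested in three grades, or about 103 pupils per school if grades are equal. Its error lies between the two columns.

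The article also promises no confidence intervals from the ANOVA, so the remark about intervals applies only to any that are reported.

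**Conclusion.** The concern holds. As written, the ANOVA omits the randomised unit and stands beside a mixed model for the same contrast with no order between them. It is also the only effect analysis named for the secondary outcomes.

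Over an assumed change-score ICC of 0.005 to 0.05, the true type I error of the nominal 5% test is 13% to 48% at 137 pupils per school and 9% to 35% at 68. These figures assume equal school sizes and no school-level change shared within a province; sharing would lower them. That the test ignores clustering does not depend on the assumed ICC; only the size of the error does. This should be settled before outcome data are analysed.

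**What to change.** - **Remove the repeated-measures ANOVA as an effect analysis**, with its Bonferroni comparisons. The Levene step then has no purpose and can go too.
- **State one school-clustered analysis for every primary and secondary outcome.** The simplest is a comparison of school means of change, or of baseline-adjusted posttest, by t-test with 4 degrees of freedom. The alternative is a mixed model with random effects for pupil and school and a school-by-time term, using a small-sample degrees-of-freedom correction.
- **State in advance whether province enters the model.** Allocation was one school per arm in each province. Fitting the three pairs leaves 2 degrees of freedom instead of 4.
- **Name one multiplicity correction and one software package** for this analysis.
- **Report Cohen's d with an interval that allows for clustering.**

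The change is to wording only; no extra data are needed. The price is wider, correct uncertainty. With 4 degrees of freedom the critical value is 2.78 instead of 1.96, so the interval is (2.78/1.96) x √DE times as wide as the pupil-level one. For m = 137 that is 2.3, 3.0 and 4.0 times at ICC 0.012, 0.025 and 0.05. For m = 68 it is 1.9, 2.3 and 3.0 times. The investigators should expect limited precision from six schools and say so in the protocol.

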#### Academic performance

The academic performance of the students will be measured using Integral Learning Diagnosis. For this study, only the reading test (2nd, 3rd, and 4th grades) and mathematics test (3rd and 4th grades) were used, measured at the beginning and end of the school year. The reading and mathematics tests measure acquired learning as defined by the curriculum update established for 2023–2025. The reading test assesses the ability to locate, interpret, relate, and reflect. For mathematics, thematic axes are evaluated according to the level (National Education Agency, 2022).

The assessments will be conducted by a trained teacher, supervised by the research team. Teachers will not know the assignment to either study group, thus ensuring an impartial procedure. In addition, assessments will be conducted in person and in locations with optimal privacy, temperature, and humidity conditions (Table 2). Furthermore, parents will complete a sociodemographic form recording the sociodemographic, health, habits, and dietary characteristics of the students (Table 2).

**TABLE 2 T2:** Variables, instruments and administration characteristics.

Category	Variables	Instruments	Administered by	Performed By	Time of assessment	
					Baseline Assessment	Final assessment
Sociodemographic	Health, habits, and dietary consumption, characteristics of the students and parents	Sociodemographic Information Form	Autofill	Parents or guardians of students in 1st, 2nd, 3rd, and 4th grade	x	
School climate	School social climate	School climate scale (ECLIS)	E. C. Teacher trained by the research team	Students in 3rd and 4th grade	x	x
Mental health	School self-esteem	School Self-Esteem Test (SSET)	Autofill	Teachers of students in 1st, 2nd, 3rd, and 4th grade	x	x
	Socioemotional wellbeing	Self-report of socioemotional wellbeing	Autofill	Teachers of students in 1st and 2nd grade	x	x
	Socioemotional wellbeing	Comprehensive Learning Diagnosis (DIA) (Evaluative socioemotional activity)	Autofill	Teachers of students in 1st, 2nd, and 3rd grade	x	x
		Comprehensive Learning Diagnoses (DIA) (Socioemotional questionnaire)		Teachers of students in 4th grade	x	x
School performance	Mathematical performance	Comprehensive Learning Diagnosis (DIA) (mathematics test)	Autofill	Teachers of students in 1st, 2nd, and 3rd grade	x	x
	Reading performance	Comprehensive Learning Diagnosis (DIA) (reading test)		Teachers of students in 2nd, 3rd, and 4th grade	x	x

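### Two unreconciled missing-data rules, multiple imputation and missForest; the second, as described, analyses predicted values as if observed and tends to understate uncertainty

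*Protocol article*

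**What the plan says.** The Statistical analysis section opens with: "Missing data will be handled using intention-to-treat analysis (multiple imputation method"). The same paragraph then specifies the comparison in SPSS: "A two-way repeated measures analysis of variance (ANOVA) will be used to determine the effects of the interventions", with group, time and their interaction.

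The next paragraph starts again on the same subject: "Missing data will be handled by a non-parametric missing value method using a random forest via the R package" missForest. It explains the method as "using a random forest trained on observed values that predict missing values". It gives no number of imputed data sets, no repeated runs and no rule for combining results.

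A third paragraph, with Jamovi as software, brings in the models for the primary outcomes: "Mixed model analyses will be carried out to establish differences in school climate and mental health between the experimental group" and the control group. These have a random effect for school. On the error rate the section says: "For all analyses, a significance level of *p* < 0.05 was established".

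**The concern.** Both missing-data sentences are unrestricted, and neither refers to the other. They cannot both produce the primary result. Someone holding the data would have to choose between them, and nothing prevents that choice from being made after the results are seen.

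The two rules also differ in validity. Multiple imputation with pooling carries the uncertainty about the missing values into the standard error. A single completed file of predictions does not. Each filled value sits on the prediction surface without residual scatter, and there is no between-imputation variance. The analysis then counts every filled row as a full observation. Standard errors come out too small, and a true null is rejected more often than the stated 0.05. With "A multicenter randomized controlled trial involving 823 students from 1st to 4th grade (6–10 years old), six schools (three intervention and three control"), there is little room for a further source of anti-conservatism.

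**Working it through.** **Text comparison.** Rule 1 is multiple imputation; rule 2 is forest prediction. Both apply to missing data in general. Position on the page suggests one pairing: rule 1 with the SPSS ANOVA beside it, rule 2 with the mixed models that follow it. The article does not say so. Under that pairing, school climate and mental health, the primary outcomes, would get the method without pooling.

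**Is there a plan figure to reproduce?** No. The article gives no attrition rate and no calculation on this point, so what follows is illustrative.

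**Inputs.**
- Alpha 0.05 from the Statistical analysis section; two-sided is assumed.
- About 205 pupils per arm: 823 / 2 arms / 2 = 206 if grades and arms are equal in size, because Table 2 limits the school climate scale to "Students in 3rd and 4th grade".
- Assumed: fraction f of post-tests missing = 10, 20 or 30%, completely at random; pre-post correlation r = 0.3, 0.5 or 0.7; no clustering; no treatment effect.

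**Closed form for the Time x Group contrast.** With two time points this contrast equals a comparison of change scores. Take unit variances and fill each missing post-test with its regression prediction from arm and baseline. Leaving out the common factor 2(1 - r)/n:
- Apparent variance: 2 - f(1 + r).
- True variance: (1 - r) + (1 + r)/(1 - f).
- SE ratio q = sqrt(apparent / true); type I error = 2 x [1 - Phi(1.96 q)].

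Worked case, r = 0.5 and f = 0.20: apparent 2 - 0.30 = 1.70; true 0.50 + 1.50/0.80 = 2.375; q = sqrt(1.70/2.375) = 0.846; type I error 2 x [1 - Phi(1.658)] = 9.7%.

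| Missing | q, r = 0.3 / 0.5 / 0.7 | Type I error |
|---|---|---|
| 10% | 0.934 / 0.924 / 0.914 | 6.7 / 7.0 / 7.3% |
| 20% | 0.865 / 0.846 / 0.827 | 9.0 / 9.7 / 10.5% |
| 30% | 0.794 / 0.766 / 0.739 | 12.0 / 13.3 / 14.8% |

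**Simulation of the same set-up** (205 per arm, 2000 runs per cell). Single conditional-mean filling gave 7.1-7.4%, 9.0-11.0% and 11.3-14.2% at 10, 20 and 30% missing, in line with the formula. Multiple imputation with 20 sets and Rubin's rules gave 4.3-5.8% throughout, with the mean standard error at 0.96-1.02 of the true value.

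**Random-forest filling** (a scikit-learn forest as a stand-in for missForest, 205 per arm). With r = 0.5 and 1000 runs, type I error was 6.2 / 6.4 / 7.5% and the SE ratio 0.96 / 0.91 / 0.88. A second simulation of 200 runs gave 6.5 / 9.0 / 12.0%. The direction agrees; the size depends on the forest settings.

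**With schools** (3 v 3 schools of 68 pupils, assumed ICC 0.02 and 0.05, school-level test). With school among the imputation predictors, type I error was 4.6-5.3% even at 30% missing. With only arm and baseline as predictors it was 6.7-12.3%.

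**The case against.** The strongest reply is that this is an unreconciled pair of sentences in a condensed article, and that the damage depends on facts not given. Much of that stands. If few post-tests are missing the effect is small. A forest can do less harm than conditional-mean filling. In the six-school design the inflation disappeared in simulation when school was a predictor. What the reply does not remove is the conflict itself: the article states two general rules, and that is not the same as leaving a detail to an analysis plan.

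Several stronger readings are tempting and not supported:
- A reader might infer that arm is left out of the forest, which would dilute the treatment effect, or that school and class are ignored. The article lists no predictors, so neither can be claimed.
- A reader might infer that outcomes not scheduled in a grade, such as school climate in grades 1 and 2, would be filled in. Table 2 restricts instruments by grade, and nothing suggests imputing outside those grades.
- A reader might take the SE ratio to be simply 1 - f, giving 7.8 / 11.7 / 17.0% at 10 / 20 / 30% missing. That fits a baseline-adjusted comparison; the planned Time x Group contrast is milder.
- A forest run with other settings (200 runs) reached 21.5% at 30% missing. Neither forest simulation above reproduced that, so it should carry no weight.
- Describing imputation as intention-to-treat is loose wording, but the intended handling in that sentence is clear.

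**Conclusion.** The point holds in this form: two general missing-data rules are stated and not reconciled, and the second, followed as written, analyses predictions as observed values. The contradiction rests on the text alone and needs no assumption. That missForest yields a single completed file is inferred from the description of predictions replacing gaps and from the absence of a pooling step; the article does not use the word single.

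The direction of the error, standard errors too small, is confirmed by formula and simulation. Its size is conditional. Under the assumed attrition, and without clustering, it is about 7% at 10% missing, 9-11% at 20% and 11-15% at 30% for conditional-mean filling, and roughly 6-12% over the whole range for a forest. These figures isolate the imputation step and do not estimate this trial's error rate, which also depends on the imputation predictors and on how schools are handled. The case for acting rests on the contradiction and on the low cost of removing it.

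**What to change.** Name one primary missing-data method for the group comparison, before analysis. Either of these would do:

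1. The likelihood-based mixed model on all observed data, with pupils analysed in the arm to which their school was allocated. The model should link a pupil's two measurements, so that the pre-test of a pupil without a post-test still contributes.
2. Multiple imputation with arm, school and baseline in the imputation model, and results pooled by Rubin's rules.

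Remove the missForest paragraph, or keep it with an explicit label as a sensitivity analysis. State which analyses the chosen method serves.

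The cost is a change of wording and slightly more analysis work. No change to recruitment, measurement or the intervention is needed.

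### The school-climate and mental-health analysis ties the intervention effect to no single between-arm contrast; naming the baseline-adjusted post-test difference would settle this cheaply

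*Protocol article*

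**What the plan says.** The Statistical analysis section of the protocol article sets out two analyses with the same three effects.

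- **ANOVA paragraph.** Its purpose is general: "A two-way repeated measures analysis of variance (ANOVA) will be used to determine the effects of the interventions". The terms are then listed: "The model effects are group (TG; CG), times (Pretest; Posttest), and their interaction over time (Time x Group"). The follow-up rule is: "The Bonferroni *post hoc* test will be applied to identify statistically significant comparisons".
- **Mixed-model paragraph, for the primary outcomes.** Its purpose is narrower: "Mixed model analyses will be carried out to establish differences in school climate and mental health between the experimental group" and the control group. The terms are: "The fixed effects of the model are group (Experimental versus control), times (Pretest; Posttest), and their interaction over time (Time x Group"). The follow-up rule is: "Post-hoc tests will be performed using Holm’s correction for multiple comparisons". On the level of significance: "For all analyses, a significance level of *p* < 0.05 was established".

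Neither paragraph names the pairs to be compared post hoc, and neither says which term or contrast is the test of the intervention. The Variables and instruments section has the outcomes measured in all participants before and after the intervention, so a pretest value is planned for each score.

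**The concern.** A two-arm trial with a pretest and a post-test has one question to answer for each score: did the arms differ after the programme by more than they would have without it? One between-arm contrast with one degree of freedom answers it. Here three model effects and an open set of post-hoc comparisons stand side by side at the same significance level.

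The candidates are not interchangeable. Some estimate the intervention effect, one estimates half of it, and others mix it with change over time that both arms share. If the choice is left open, the reported result can rest on a diluted or non-randomised comparison although a better one is available from data already planned.

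**Working it through.** The plan gives no figure of its own on this point, so there is none to reproduce. The check asks what each candidate estimates and how precisely.

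**Inputs from the protocol article.** Two arms and two time points; effects group, time and Time x Group; allocation by randomisation of schools, so the expected pretest difference between arms is zero.

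**Assumptions, not in the documents.** SD of 1 at both times; pre-post correlation r of 0.5 to 0.7; n pupils per arm; clustering left out. For that reason only ratios between contrasts are used, not power levels.

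**Step 1: what each candidate estimates.** Let δ be the intervention effect at post-test and τ any change common to both arms. Relative to the pretest mean, the expected cells are: control pre 0, control post τ, experimental pre 0, experimental post τ + δ.

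- Group main effect: (0 + δ)/2 = δ/2
- Time main effect: (τ + τ + δ)/2 = τ + δ/2
- Time x Group: (τ + δ) − τ = δ
- Arm difference at post-test, with or without pretest adjustment: δ
- Within-arm change, experimental: τ + δ
- Within-arm change, control: τ

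Only Time x Group and the arm difference at post-test estimate δ itself. Every within-arm change contains τ.

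**Step 2: pupil-level variances.**

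- Time x Group: 4(1 − r)/n
- Post-test difference adjusted for pretest: 2(1 − r²)/n
- Group main effect: (1 + r)/n, for a target of δ/2

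**Step 3: adjusted post-test difference against Time x Group.** Both estimate δ, so their variances compare directly:

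2(1 − r²) / [4(1 − r)] = (1 + r)/2

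- r = 0.5: 0.75, which is 25% less variance
- r = 0.6: 0.80, which is 20% less
- r = 0.7: 0.85, which is 15% less

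**Step 4: cost of the diluted group effect.** Squared signal over variance is (δ/2)² × n/(1 + r) = nδ²/[4(1 + r)] for the group effect and nδ²/[4(1 − r)] for Time x Group. The ratio is (1 − r)/(1 + r):

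- r = 0.5: 0.5/1.5 = 0.33
- r = 0.6: 0.4/1.6 = 0.25
- r = 0.7: 0.3/1.7 = 0.18

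At pupil level, then, the group main effect carries between about a sixth and a third of the information that Time x Group carries about the same δ.

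**The case against.** **The article is a condensed text, and a full analysis plan may name the contrast.** This largely stands. Silence alone would be missing detail. What remains is that the article fixes the terms, the post-hoc rules and the level, and that a more precise contrast is available at almost no cost.

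**The mixed model's stated aim is a difference between groups.** This stands. It rules out the time effect as the primary answer in that paragraph. The group effect, Time x Group and a post-test comparison all still fit the aim.

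**A reader might infer that an ordinary school-year trend will be reported as the programme's effect.** The documents do not support that. Assume a common trend of 0.2 SD, 205 pupils per arm, r = 0.6, no clustering and Bonferroni over all six cell pairs. The experimental pre-post comparison is then significant in about 71% of trials with no effect (0.2/√(2 × 0.4/205) = 3.20 against a critical value of 2.64). If post-hoc tests are read only after a significant Time x Group, the figure falls below 3%. The article fixes neither reading, lists no six pairs and gives no trend.

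**A reader might infer that the group main effect inflates false positives.** It does not: on its own it keeps its 5% level, and its fault is dilution. If either it or Time x Group could count, the rate would be about 1 − 0.95² = 9.75%, but no sentence states such a rule.

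**A reader might see a conflict between Bonferroni and Holm.** The two corrections belong to different models in different paragraphs, so one p-value need not face both rules.

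**The choice between the adjusted difference and Time x Group is partly preference.** Both estimate δ. The adjusted difference is the more precise at pupil level, but Time x Group is an acceptable alternative.

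**Conclusion.** The point holds as a cheap improvement, not as an error in the model. The section leaves open which between-arm contrast decides each school-climate and mental-health score. Among the results it lists, the group main effect estimates half the post-test effect, and within-arm changes are not randomised comparisons.

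The gain from the adjusted post-test difference is 15% to 25% less pupil-level variance than Time x Group. It rests on assumed pre-post correlations of 0.5 to 0.7 and equal SDs at the two times. It says nothing about the between-school component, so no power level for a trial of six schools should be read from it. Whether the standard error of Time x Group is right is a separate question.

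**What to change.** In the mixed-model paragraph of Statistical analysis, add wording such as:

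*For each school-climate and mental-health score measured at pretest and post-test, the effect of the intervention is judged by one contrast: the experimental-minus-control difference at post-test, adjusted for the pupil's own pretest score, with school as cluster. Group and time main effects and within-arm changes are reported descriptively, without claims of significance.*

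If the repeated-measures model is kept, name Time x Group as the only deciding term, with the same statement about the other effects. With one deciding contrast per score, post-hoc pairwise testing has no role in the decision.

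The wording is limited to scores with a pretest and a post-test because the Mental health section places the Integral Learning Diagnosis at three points in the school year. That instrument needs its deciding time point stated.

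The cost is a few sentences and no new data, since the pretest is already planned. The small downside is that improvements within one arm can no longer be presented as significant findings.
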